# Advancing spatial repellents for malaria control: effectiveness and cost-effectiveness of a spatial repellent under operational use in Northern Uganda—study protocol for a cluster randomized controlled trial

**DOI:** 10.1186/s13063-024-08378-1

**Published:** 2024-08-22

**Keywords:** Malaria, Spatial repellent, Transfluthrin, Vector-borne diseases, Mosquito vectors, Incidence

## Abstract

**Background:**

Spatial repellents (SRs) have been widely used for the prevention of mosquito bites, and preliminary findings suggest efficacy against both malaria (1) and *Aedes*-borne viruses (2) but their effectiveness in reducing mosquito-borne diseases under operational use has never been evaluated. SRs have the potential of being critical tools in the prevention of mosquito-borne diseases in contexts where typical vector control strategies, such as insecticide-treated nets (ITNs) and indoor residual spraying, are inaccessible or underutilized such as among displaced persons or in emergency relief settings.

**Methods:**

Children will be enrolled in 3 separate cohorts to establish the effectiveness of SRs in reducing malaria infection in different distribution channels. One cohort will estimate the direct effect of the SR distributed through a reference channel (study personnel distribution). The two remaining cohorts will estimate the protection of the SR distributed through a voucher channel and the Village Health Team channel. Cohorts will be followed twice a month (approximately every 15 days): during the first scheduled household visit in the month, a blood sample will be taken for malaria rapid diagnostic test (Monthly Visit #1); and, during the second scheduled household visit, a blood sample will only be taken if the participant has a recent history of fever (Monthly Visit #2). The incidence of malaria in each cohort will be estimated and compared to the reference cohort to determine the benefit of using a SR in an area with high, year-round transmission of malaria.

**Discussion:**

This study will address the knowledge gap of whether or not SRs are effective in reducing human malaria disease in humanitarian assistance and emergency response settings in sub-Saharan Africa where underlying transmission rates are historically high and ITNs may or may not be widely deployed. This research will inform policy makers on whether to recommend SRs as a means to further reduce malaria transmission for such operational programs.

**Trial registration:**

ClinicalTrials.gov NCT06122142. Registered on November 8, 2023.

## Introduction

### Background and rationale {6a}

Spatial repellents (SRs) are a promising new vector control paradigm that could add to the existing armamentarium for malaria prevention [1, 2]. SRs such as mosquito coils have been shown to reduce mosquito biting [3, 4]and, in studies conducted in Indonesia [5, 6] and China [7], to reduce malaria transmission in human populations. Recently, SRs have also been proven to reduce *Aede*s-borne viruses [8]. Although the value of SR is applicable across a wide range of scenarios, evidence is required to demonstrate the effectiveness of SRs under operational use conditions. One scenario in which SRs have potential for significant impact is in humanitarian relief efforts. People who have been displaced due to conflict or environmental disasters very often arrive in an exhausted, weakened, traumatized state, already suffering from or vulnerable to infectious diseases and malnutrition. They may lack access to health services and health commodities such as insecticide-treated nets (ITNs), and temporary structures to accommodate them are often substandard or semi-enclosed, providing little protection from mosquitoes.

As of 31 March 2023, the United Nations High Commissioner for Refugees has registered 1,532,168 refugees in Uganda, of which 867,391 are from South Sudan and 487,044 are from the Democratic Republic of Congo. Uganda has a unique refugee policy, whereby refugees are given a 30 × 30 plot to construct their structures and farm on this land. Refugees are placed into different areas based on their date of arrival. Refugees live among host communities in the same area and have equal access to health facilities and other services.

Malaria is highly endemic throughout all of Uganda and accounts for 31.1% (14,381,183/46,261,118) of all reported outpatient visits and 25% (844,965/3,385,664) of all admissions, placing a heavy burden on the health care system [9]. This is especially true in the north of the country, where fighting in South Sudan has displaced tens of thousands of South Sudanese people who have been forced to seek refuge in northern Uganda. The prevalence of malaria according to rapid diagnostic test (RDT) in all refugee settlements across the nine hosting districts was 36.6% for children 6–59 months [10]. Refugees live in grass thatched roof houses or in tarpaulin structures, and at times in areas of rapid over-growth that provide ample breeding space for mosquitoes.

Along with many other multilateral and international organizations, Catholic Relief Services (CRS) provides humanitarian assistance to victims of natural and man-made emergencies across the world, including three longstanding conflicts in Uganda. Because of the high burden of malaria and the history of CRS’ efforts in this region, the site was selected to evaluate the effectiveness of a new SR product formulated to last up to 1 month for the prevention of malaria using a cluster randomized control trial (cRCT) study design. The study will enroll children 6 months to 59 months of age as study participants into three separate cohorts and followed to determine the time to first malaria infection with monthly RDTs. The study will include separate cohorts to measure the direct effect of SRs as well as the protection to participants using varied distribution channels: paid study personnel (reference arm-positive control), Village Health Teams (VHTs), and a voucher system. The voucher system will be modeled based on CRS’ past experience using vouchers in bed net distributions and emergency response programs.

This evaluation will serve as an effectiveness trial of SR products for sub-Saharan Africa emergency response and recovery contexts. Evidence will inform health impact and equivalence of impact through different ‘real-life’ delivery systems for donor market introduction. The cRCT will evaluate operational effectiveness against malaria infections in a rural African environment linked to displaced persons where ITNs and indoor residual spraying (IRS) may be constrained. Findings and operational use guidance will be submitted to the World Health Organization (WHO), in coordination with the Ministry of Health (MOH) in Uganda.

Despite the scale-up of effective tools for the prevention and control of malaria, this disease remains one of the primary causes of morbidity and mortality in sub-Saharan Africa. New tools are needed to address the threat of insecticide resistance and outdoor biting vectors and to sustain the drive to elimination. SRs such as mosquito coils have been shown to reduce mosquito biting [3, 4] and, in studies conducted in Indonesia [6] and China [7], to reduce malaria transmission in human populations. Recently, SRs have also been proven to reduce *Aede*s-borne viruses [8]. The WHO has developed methods to evaluate the efficacy of new SR products; however, the effectiveness of an SR intervention delivered under programmatic conditions has not been evaluated. It is unlikely that efficacy estimates derived from tightly controlled phase III trials will be realized in program settings. This study will address the knowledge gap of whether or not SRs are effective in reducing human malaria disease in humanitarian assistance and emergency response settings in sub-Saharan Africa where underlying transmission rates are historically high and the use of ITNs may be challenged. This research will inform policy makers on whether to recommend SRs as a means to further reduce malaria transmission for such operational programs.

### Objectives {7}

The primary objective of the study is to demonstrate and quantify the effectiveness of a SR product, in reducing malaria infection in human cohorts under operational program conditions. The design will be a prospective cRCT representing an operational research study.

To compare the effectiveness of SR against malaria infection (both first-time and recurrent) between each of the two operational program delivery mechanisms (1. VHTs delivering SR directly to participants (VHT); 2. participants redeeming a voucher for SR at a central location and applying it in structures themselves (Voucher)) vs a reference distribution channel (positive control; study team personnel delivering product directly to participants at their homes).

Secondary objectives are (1) to estimate the cost-effectiveness of SR distribution by each distribution channel (VHT and Voucher) compared to the reference distribution channel, and (2) assess the safety of the SR product.

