### Relevant concomitant care permitted or prohibited during the trial {11d}

While the standard-of-care for clinical management of malaria and vector control interventions (e.g., ITNs, IRS) will not be withheld in any of the distribution channels, these interventions will be monitored and recorded throughout the study. ITNs continue to be distributed through mass campaigns every 2 years with the latest distribution conducted in early December 2023 in Yumbe District, where the Bidibidi Refugee Settlement is located. ITNs are also distributed regularly to pregnant women during antenatal and postnatal care services at health facilities in the Bidibidi Refugee Settlement, and to children under five during expanded immunization programs. IRS started in December 2022 and is expected to occur annually, with the latest conducted in December 2023. At enrollment, eligible children will be provided a treatment dose of artemether-lumefantrine (AL) free of charge for malaria parasite clearance and a new ITN. In addition, study participants will be provided treatment for malaria infection throughout the follow-up period. Participants will be encouraged to continue ITN use and not instructed to avoid alternative vector control tools (e.g., coils, topicals, aerosol sprays, repellents) which will allow for an estimation of the SR effect assuming all other measures are still occurring for malaria prevention, essentially providing insight on an additive benefit above that provided by currently recommended WHO malaria preventive measures.

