## Assignment of interventions: allocation

### Sequence generation {16a}

The unit of randomization for the SR intervention delivery channel will be a cluster. The study statistician will have access to malaria prevalence and census data that will be collected during the ramp-up phase of the study and may be used to inform potential stratification prior to randomization. Criteria for stratification will be malaria prevalence levels and/or demographic endpoints. Following stratification (as needed), clusters will be allocated to receive the SR product either through delivery by study personnel (reference arm, positive control), VHTs, or vouchers using a random number generator (https://www.random.org). The cluster allocation code will be made available to the DSMB for use in safety assessments. The site database manager will assign a unique HH identification number (HIN) to each HH for use in monitoring malaria infections during the trial and the site intervention administrator will coordinate SR product distribution to mitigate stock-out. Following cluster allocation, a total of 45 households will be randomly selected per cluster. In HHs with multiple children that meet the study inclusion criteria, all eligible children will be invited to participate; however, only one will be enrolled. The methods used for this randomization will be the rand() function from Excel for households and the random.sample() function for age-eligible members.

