### Concealment mechanism {16b}

The Sponsor, study Principal Investigator (PI), and staff will not be blinded to cluster assignment (SR delivery channel). There will be no placebo integrated into the study design, as the SR intervention will have already been evaluated for efficacy under controlled conditions. Ethical approvals and census and mapping activities were conducted prior to the allocation. However, cluster allocation was shared with the study team prior to recruitment and enrollment to allow the identification of distribution points within clusters in the voucher arm and the recruitment of VHTs within the VHT arm.

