#### Enrollment of the cohort

A cohort of children aged ≥ 6 months to ≤ 59 months will be enrolled within each cluster to assess the effectiveness of the SR product against the contemporaneous control and in additional clusters to estimate effectiveness using programmatic delivery systems. HHs will be randomly selected from the master list of HHs obtained during ramp-up phase mapping to achieve the desired sample size.

Selected HHs based on cluster maps will be visited and if a child is present, the study will be explained and consent obtained from the child’s primary caregiver before screening for eligibility and enrolling him/her in the study. All eligible children in a selected HH will be invited to participate. (See above for a more complete description of the consent process.) At enrollment, the study team will have a list of all age-eligible children in each HH selected. These data will have come from the initial mapping and census of the study clusters. At the time of participant recruitment, the tablet will randomly select one of the age-eligible children for the field staff to screen for inclusion and exclusion criteria, which includes a hemoglobin test. Prior to screening, the team will obtain parental/caregiver consent. If there are no eligible children in the HH after screening, a new HH will be randomly selected from the HH listing exercise (mapping and census).

At enrollment, the age and gender of the child will be recorded and the parent/guardian (as needed) will be asked about the use of ITNs and anti-malarial drugs. Contact information, as available, will be captured. A fingerstick blood sample will be taken for a malaria RDT, and a hemoglobin level will be evaluated in a capillary sample using the HemoCue device**.** The study team will work with local health partners and the district health department providing iCCM to make sure children in need of iron supplements and antihelminths are managed according to national protocols and coordinate any referrals or follow-ups as needed. If the screened child does not meet the inclusion criteria, the tablet will randomly select another child from the remaining age-eligible children in the same house. The process will continue until one of the children is successfully enrolled.

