All children enrolled in the study will be provided an ITN. This will allow us to measure the added benefit of SR product above that provided by currently recommended preventive measures. In addition, a blood sample will be taken for a RDT for all participants enrolled in the cohort to be used as a baseline data measure. All participants (regardless of RDT results) will be provided a treatment dose of artemisinin-combination treatment (ACT) AL at the start of the study prior to receiving SR, to clear any prepatent or patent malaria parasites, unless they have recently been treated (within the last 2 weeks). Participants will be treated according to RDT results throughout the study period, according to national protocols.

The enrollment period will take approximately 1 month, during which time incidence of malaria disease in study clusters will be measured prior to the deployment of the study product.

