#### Cost-effectiveness

We will address issues of cost of implementation by evaluating efficacy in relation to coverage using varied delivery systems. The cost of manufacturing the SR intervention by SCJ will be monitored and documented to model affordable pricing by industry stakeholders to produce next in class SR products ensuring efficacious options for procurement by donor agencies and countries. Projected cost per person protected will comprise product costs based on models using project data (epidemiological, and market) and operational costs. Treatment cost averted using ITNs vs ITNs + SR to the global scale is required for estimating the economic impact. The study will measure the cost of Mosquito Shield implementation in relation to manufacturing, efficacy, and coverage to model projections of cost-effectiveness to incentivize procurers.

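### The objective and several sections promise the effect of the spatial repellent itself, but every arm receives it, so the randomised comparison estimates only differences between delivery channels

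*Protocol article*

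**What the plan says.** All references are to the protocol article.

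**Claims about SR itself**
- Objectives {7}, first sentence: "The primary objective of the study is to demonstrate and quantify the effectiveness of a SR product, in reducing malaria infection in human cohorts".
- Abstract, Methods: incidence in each cohort is to be "compared to the reference cohort to determine the benefit of using a SR in an area with high, year-round transmission of malaria".
- Abstract, Discussion, and Background and rationale {6a}: the study is to settle whether SR works in humanitarian settings and to guide policy makers on recommending it.
- Trial design {8}: one cohort, the reference arm, is to estimate the direct effect of SR.
- Relevant concomitant care {11d}: leaving other vector control in place is described as "essentially providing insight on an additive benefit above that provided by currently recommended WHO malaria preventive measures".
- Enrollment of the cohort: on giving every child a net, "This will allow us to measure the added benefit of SR product above that provided by currently recommended preventive measures". The same section says the cohort serves "to assess the effectiveness of the SR product against the contemporaneous control".

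**What is randomised and analysed**
- Sequence generation {16a}: "clusters will be allocated to receive the SR product either through delivery by study personnel (reference arm, positive control), VHTs, or vouchers".
- Concealment mechanism {16b}: "There will be no placebo integrated into the study design". Who will be blinded {17a} repeats this.
- Objectives {7}, second paragraph, and Outcomes {12}: each of VHT and voucher against the reference channel.
- Sample size {14}: precision is given for that same contrast, with no formal test planned.
- Statistical methods {20a}: the treatment factor has three levels (reference, VHT, voucher), and none is unexposed to SR.

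**The concern.** An effect of SR, or its benefit on top of nets, is a contrast between having SR and not having it. The claims listed above need a group without SR, and the design has none. The contemporaneous control named under Enrollment of the cohort matches no arm. Giving every child a net holds net provision constant across arms; it does not supply a net-only comparator.

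What is at stake is the conclusion. Background and rationale {6a} says the findings will go to WHO, in coordination with the Ministry of Health, and ties the trial to donor market introduction. If both channels perform like the reference, the hazard ratios will be near 1. Read against the objective's first sentence, that could be reported as showing that SR is effective under operational use. The same result would arise if SR had no effect in any arm.

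**Working it through.** **1. What the stated precision refers to.** Inputs from Sample size {14}: 16 clusters per arm, 40 households per cluster, between-cluster coefficient of variation 0.40, 10% loss, 12 months, baseline rate 0.5 to 1 per person-year. Statistical methods {20a} gives a 90% interval. One child is enrolled per household.

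Formula: var(log HR) = (2/16) × (0.40² + 1/D), where D is the expected number of first infections per cluster, D = 40 × 0.9 × (1 − exp(−rate)). Bounds at HR = 1 are exp(±1.645 × SE).

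| Rate | D | SE | 90% bounds |
|---|---|---|---|
| 0.5 | 14.2 | 0.170 | 0.756 to 1.322 |
| 1.0 | 22.8 | 0.160 | 0.769 to 1.300 |

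The article gives lower bounds of 0.75 to 0.77 and upper bounds of 1.30 to 1.33. The two agree to within about 0.01. (The article pairs the wider interval with the higher rate, whereas this formula gives the reverse; that does not affect the present point.) The calculation uses two SR-treated arms, so the stated precision belongs to a channel-versus-reference hazard ratio and to nothing else.

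**2. What the planned hazard ratios say about SR.** Let λ₀ be the rate without SR, E the proportional reduction from SR where it is in effective use, and c the effective coverage in an arm. Treat the arm rate as λ₀(1 − E·c). Then

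HR(channel vs reference) = (1 − E·c_channel) / (1 − E·c_reference).

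λ₀ cancels, and no arm observes it. With equal coverage in the arms, HR = 1 whatever E is. Illustration with c = 1 in every arm and an assumed λ₀ of 1.0 per person-year:

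| Assumed common SR effect | Rate in each arm | HR VHT/reference | HR voucher/reference |
|---|---|---|---|
| 0% | 1.0 | 1.00 | 1.00 |
| 20% | 0.8 | 1.00 | 1.00 |
| 30% | 0.7 | 1.00 | 1.00 |
| 50% | 0.5 | 1.00 | 1.00 |

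The arm rates differ between rows, but they reveal E only if λ₀ is known, and the trial does not measure λ₀ in a concurrent group.

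**3. Whether another part of the plan supplies λ₀.** Enrollment of the cohort mentions measuring incidence for about one month before SR is deployed. At most this allows an uncontrolled before-after comparison, and the article plans none. It would be confounded by season, by new nets, by parasite clearance (given to all children except those treated in the previous 2 weeks), and by annual indoor spraying. Households in the clusters that are not selected are not enrolled in the cohort, so they are no comparator either.

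**The case against.** The strongest reply is that the operative plan is consistent. The second paragraph of the Objectives, the outcome, the precision calculation and the model all address channel versus reference, and the first sentence can be read as a general aim. The article also explains the missing placebo: efficacy will have been evaluated elsewhere under controlled conditions. The reference arm is labelled a positive control, and the Discussion presents the study as a complement to efficacy trials, centred on delivery.

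Most of this stands. It means the design and analysis need no repair, and it gives a reason for having no placebo arm. It does not rescue the claims. External efficacy may be assumed, but this trial then neither demonstrates nor quantifies it. Background and rationale {6a} itself doubts that phase III efficacy will be realised in programmes, so it cannot simply be carried over.

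Three stronger readings are tempting, and the article does not support them:
- *The trial holds no information at all about SR.* This goes too far. If a channel lowers coverage and its hazard ratio exceeds 1, that is indirect evidence that SR works, and the per-protocol models plan application rate and coverage as covariates. Such evidence is not a randomised SR contrast, and VHTs also give malaria-prevention education, so a channel difference need not come from SR.
- *The Cost-effectiveness section claims to measure nets against nets plus SR.* It says "Treatment cost averted using ITNs vs ITNs + SR to the global scale is required for estimating the economic impact" and speaks of models and projections. What it leaves open is where the efficacy input comes from.
- *The stated bounds set a threshold of SR efficacy below which the trial fails.* That would require a channel that delivers nothing. It is a question of channel sensitivity, and an unlikely extreme: staff supply the first month's product in the voucher arm, and VHTs visit monthly.

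**Conclusion.** The point holds as a contradiction between stated claims and design. The first sentence of the Objectives, the Abstract, Background and rationale {6a}, Trial design {8}, Relevant concomitant care {11d} and Enrollment of the cohort attribute to the trial a result that no randomised contrast in it can give. The size is structural rather than numerical: both planned hazard ratios are 1.00 for every common SR effect from 0% to 50% in the illustration, and algebraically for any common effect below 100%. That result assumes equal effective coverage in the arms. With unequal coverage the hazard ratios move, but they still do not estimate SR against no SR.

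The wording should be corrected before results are reported, because it determines what the trial may conclude. A reader might infer that the trial is wrongly designed; the article does not support that, since the channel-versus-reference question is well posed and the outcome, precision calculation and model all match it.

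**What to change.** 1. Restate the primary objective, the Abstract, Background and rationale {6a}, Trial design {8}, Relevant concomitant care {11d} and Enrollment of the cohort as: estimate the relative incidence of malaria infection under VHT and voucher delivery of SR compared with delivery by study personnel.
2. Delete or correct the reference to a contemporaneous control.
3. State once, plainly, that SR versus no SR is not estimated by randomised comparison in this trial.
4. In Cost-effectiveness and in the costing paragraph of Statistical methods {20a}, state that any SR-attributable effect, cases averted, or cost comparison of nets with nets plus SR is modelled from an external efficacy estimate, with its uncertainty carried through, and is not measured here.

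The arms, sample size, outcome and primary model stay as they are. The cost is a protocol wording change and a narrower claim.
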